## 9.2 Exclusion Criteria

1. Participants who are receiving any other investigational agents.
2. Primary sites of malignancy in oral cavity or major salivary gland or nasopharynx or skin
3. More than Six months post completion of CTRT
4. Patients with QTc prolongation defined as QTc interval greater than 480 ms in view of risk of sudden cardiac death associated with use of celecoxib.
5. Patients receiving methotrexate for other indications not limited to rheumatoid arthritis
6. Patients who had received long term Cox-2 inhibitors ( more than 3 month continuous usage) will be excluded
7. History of allergic reactions attributed to compounds of similar chemical or biologic composition to any agents used in study.
8. Uncontrolled intercurrent illness including, but not limited to, hypertension, tuberculosis, diabetes, ongoing or active infection, symptomatic congestive heart failure, unstable angina pectoris, cardiac arrhythmia, renal failure (on dialysis), active gastrointestinal bleeding, cerebrovascular accidents, inflammatory bowel disease, known hyperkalemia ( CTCAE version 4.02 grade 3 or above which is persistent over 1 week) or psychiatric illness/social situations that would limit compliance with study requirements.
9. Pregnant women and breastfeeding women are excluded from this study because celecoxib / erlotinib and methotrexate are agents with the potential for teratogenic or abortifacient effects. Because there is an unknown but potential risk for adverse events in nursing infants. These potential risks may also apply to other agents used in this study.
10. HIV-positive, Hepatitis B and C seropositive patients are excluded from this study.
11. Patients with previous history of other cancers within last 2 years

# 10 Interventions

## 10.1 Registration

Subjects must meet all of the inclusion criteria and none of the exclusion criteria to be eligible for this trial/study. There will be no exceptions made to these eligibility requirements at the time of registration.

Subjects must be registered before starting study treatment. Treatment should be planned to start within 30 days after registration.Once the registration process has been completed, the subject will be assigned a subject study number, and written confirmation of registration will be provided to the site. Individuals only be registered once in this trial. Following which the patient would be randomize. The randomization procedure is explained in “ Allocation of arm” section.

## 10.2 Arm A

In arm A **observation** would be done. The schedule of observation will be in accordance with the institutional follow up protocol which is as below

**First year** : Patient would be followed up at 3 monthly intervals. Clinical history and examination would be done. Blood investigations like complete hemogram, renal function tests and TSH would be done. FACIT QOL H&N would be filled at baseline,6 and at 12 months. The blood of patients of 10 ml would be collected at baseline, first follow up and at progression in both arms for future research purpose

**Second year** : Patient would be followed up at 3 monthly intervals. Clinical history and examination would be done. Blood investigations like complete hemogram, renal function tests and TSH would be done sos. FACIT QOL H&N would be filled at 18 & 24 months

**Third year-Fifth year** : Patient would be followed up at 6 monthly intervals. Clinical history and examination would be done. Blood investigations like complete hemogram, renal function tests and TSH would be done sos.

**Post fifth year** : Patient would be followed up at 1 year intervals. Clinical history and examination would be done. Blood investigations like complete hemogram, renal function tests and TSH would be done SOS.

## 10.3 Arm B

In arm B **adjuvant metronomic** would be administered.

### 10.3.1 Schedule

Metronomic chemotherapy is the study intervention in this trial. The metronomic chemotherapy constitutes of methotrexate and celecoxib.

Oral methotrexate tablet 15 mg/m2 will be self administered weekly ie on D1,D8, D15 and D22 of every 28 day cycle.

Capsule celecoxib would will be self administered twice daily in a dose of 200 mg BID continuously .

The combination will be continued to a maximum of such 18 cycles; unless prohibitive toxicity or disease progression occurs prior to it. The schedule of visits of these patients would be similar to that in observation arm. Except that ECG and LFT would be done at each visit.

### 10.3.2 Administration

Lowest strength Methotrexate tablet is available as a 2.5 mg tablet. The recommended dose should be rounded to the nearest lower multiple of 2.5 mg. All tablets should be taken with at least half a glass of water one hour prior to or two hours post food. Capsule celecoxib should be taken twice daily 12 hours apart one hour post meal.

### 10.3.3 Dose modifications

Instructions for treatment delays and dose modifications for adverse events are specified below. Adverse events will be graded according to National Cancer Institute ,Common Terminology Criteria for Adverse Events (CTCAE) version 4.03. In general, treatment should be withheld during adverse events of severity G3-4, and not restarted until the adverse event has resolved to G0-1, at the investigator’s discretion. Day 1 treatment may be delayed for a maximum of 14 days. If the adverse event has not resolved to G0-1 after delaying day 1 treatment for 14 days, then study treatment should be discontinued. Treatment should not be delayed or modified for alopecia of any grade.

Specified dose reductions apply to all subsequent doses of study drug. If a patient experiences several adverse events with differing recommendations, then the modification that results in the longest delay and lowest dose should be used. Dose escalations or dose re-escalations after reductions for adverse events are prohibited.

#### 10.3.3.1 Dose modification for hematological toxicity

| **PARAMETER** | **TIMING** | **RESULT OR PROBLEM** | **CTCAE GRADE** | **ACTION WITH STUDY TREATMENT**  **(Methotrexate unless otherwise specified)** | | | | |
| --- | --- | --- | --- | --- | --- | --- | --- | --- |
| Neutrophils  (x10^9^/L) | Previous cycle | Febrile neutropenia, or infection with neutropenia | G4 | Delay D1 until resolved AND  reduce dose of methotrexate by 20% | | | | |
|  |  |  |  |  |  |  |  |  |
|  | D1 | 1.0-1.5 | G2 | Delay D1 until ANC is >1.5 AND  If delay > 7 days but < 15days, reduce doses by 20% level.  If delay >15 days then discontinue. | | | | |
|  |  | <1.0 | G3-4 | Delay D1 until ANC is >1.5 AND  reduce doses by 20% level. | | | | |
| Platelets  (x10^9^/L) | Previous cycle | < 25 or bleeding | G4 | Delay D1 until resolved AND  reduce methotrexate doses by 20% | | | | |
|  | D1 | <100 | G1-4 | Delay D1 until platelet count is > 99 x10^9^/L AND  If delay > 7 d but <15 days reduce doses by 20% level.  If delay > 15d then discontinue. | | | | |
| Haemoglobin  (g/L) | First occasion | <80 | G2 | Transfuse to Hb > 80 g/L AND  treat as scheduled. | | | | |
|  | Second occasion | <80 | G2 | Transfuse to Hb >80, treat as scheduled, AND reduce doses of methotrexate by 20% | | | | |
| Day 1 treatment may be delayed for a maximum of 14 days. If the adverse event has not resolved to G0-1 after delaying day 1 treatment for 14 days, then chemotherapy should be discontinued.  **- No dose reduction in celecoxib recommended. However, if chemotherapy is discontinued then celecoxib should also be discontinued. | | | | |  |  |  |  |

Table 1 : Dose modification in hematological events

#### 10.3.3.2 Dose modifications for other adverse events

| System | CTCAE term | CTCAE grade | Other details | Actions with drugs | Other actions |
| --- | --- | --- | --- | --- | --- |
| Hepatic | Bilirubin | Grade 3-4 | >3.0 ULN | Discontinue methotrexate |  |
| Hepatic | AST/ALT | Grade 3-4 | >5.0 x ULN AND  > 2 x baseline | Discontinue methotrexate |  |
| Renal | Creatinine | G2-4 | >1.5 x baseline AND  > 1.5 x ULN | Withhold both methotrexate and celecoxib until <1.5 x baseline  AND then restart at 20% lower dose |  |
| Infection | Infection | G3-4 |  | Delay until G0-1  Restart when G0-1  Reduce doses by 20% of methotrexate |  |
| GI | Nausea | G3-4 |  | Delay until G0-1  Restart when G0-1  Reduce doses by 20% of methotrexate |  |
| GI | Vomiting | G3-4 |  | Delay until G0-1  Restart when G0-1  Reduce doses by 20% of methotrexate |  |
| GI | Diarrhea | G3-4 |  | Delay until G0-1  Restart when G0-1  Reduce doses by 20% of methotrexate |  |
| GI | Mucositis | G3-4 |  | Delay until G0-1  Restart when G0-1  Reduce doses by 20% of methotrexate |  |
| Cardiovascular | Myocardial infarction | G3-4 |  | Discontinue methotrexate 7 celecoxib |  |
| Vascular | Thrombo-embolic event | G3-4 | Venous ( DVT or PTE) | Delay both methotrexate & celecoxib until adequately treated  Restart at physician discretion | Anticoagulate with heparin, not warfarin, whilst on study drug |
| Vascular | Thrombo-embolic event | G3-4 | Arterial | Discontinue both methotrexate and celecoxib |  |
| Skin | Various | G3-4 |  | Delay methotrexate and celecoxib until G0-1  Restart when G0-1  Reduce subsequent doses 20% |  |

Table 2: Dose modification for non hematological toxicity

### 10.3.4 Start of a new cycle

Re-treatment on day 1 will require: haemoglobin > 8 mg/dl, ANC count > 1500/mm3, platelet count > 1 lakh/mm3, creatinine clearance rate >30 ml min, and resolution of all non haematological toxicities (except alopecia and fatigue) to baseline or less than grade 1.

If methotrexate is delayed or withheld and if the cause of the delay does not require an interruption in celecoxib then it will be continued. Subsequently methotrexate can be given on the next weekly scheduled day. The scheduled methotrexate which was omitted remains omitted. The cycle would be considered continued if celecoxib is continued. If both are delayed and the delay is less than 15 days then from the day of restart the remaining cycle would be completed.

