******- Blood sample will be collected only at the first 3 month visit.**

| Investigations | Baseline | D1 of chemotherapy for 18 cycles ( every 3 month in till 18 months) | Post 18 months at schedule visit | Progression |
| --- | --- | --- | --- | --- |
| History | √ | √ | √ | √ |
| Drug allergy | √ | X | X | X |
| Local examination | √ | √ | √ | √ |
| CECT neck + relevant part | X | * | * | * |
| PET-CT | √ | X | X | X |
| Toxicity assessment | X | √ | √ | √ |
| Biopsy / FNA | X | X | X | √ |
| CBC | √ | √ | √# | √ |
| RFT | √ | √ | √# | √ |
| LFT | √ | √ | √# | √ |
| SE ,Ca, Mg | √ | √ | √# | √ |
| TSH | √ | * | * | * |
| ECG | √ | √ | X | X |
| b-HCG | √ | X | X | X |
| FACT -H&N QOL | √ | ** | X | X |
| Blood sample 10 Ml ( 5 ml EDTA + 5 ml Plain) | √ | √*** | X | √ |

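### The rule for starting a new cycle needs blood results every 28 days, but the Arm B schedule, on its likelier reading, provides them only every 3 months

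*Protocol*

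**What the plan says.** **The dosing rule.** Section 10.3.4 states: "Re-treatment on day 1 will require: haemoglobin > 8 mg/dl, ANC count > 1500/mm3, platelet count > 1 lakh/mm3". The same sentence adds creatinine clearance above 30 ml/min and recovery from non-haematological toxicity. Table 1 (10.3.3.1) has separate D1 rows for neutrophils and platelets that prescribe delay, a 20% reduction or discontinuation, for example "Delay D1 until ANC is >1.5 AND". Section 10.3.1 sets the cycle: methotrexate is "self administered weekly ie on D1,D8, D15 and D22 of every 28 day cycle", for at most 18 cycles.

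**The testing schedule.** For Arm B visits, section 10.3.1 says "The schedule of visits of these patients would be similar to that in observation arm". The one addition is "Except that ECG and LFT would be done at each visit". Section 10.2 sets the observation arm's interval in both the first and second years: "Patient would be followed up at 3 monthly intervals".

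**The table.** In Table 4, the on-treatment column that ticks CBC and RFT is headed "D1 of chemotherapy for 18 cycles ( every 3 month in till 18 months".

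**Two related statements.** The haemoglobin threshold is in mg/dl in 10.3.4, while Table 1 uses 80 g/L. The maximum duration is 18 cycles of 28 days in 10.3.1, but 18 months in the concept sheet.

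**The concern.** A mandatory check at every cycle start and a 3-monthly blood schedule cannot both be followed. An investigator who keeps to the visit schedule lets 12 to 13 self-administered methotrexate doses pass between scheduled counts and creatinine (84/7 = 12; 91/7 = 13). One who keeps to 10.3.4 has to arrange tests between visits that no schedule lists.

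What is at stake is safety and uniform dosing. Asymptomatic cytopenia or falling renal function is found only by a blood test, and both trigger action under Tables 1 and 2. Patients may also enter with a creatinine clearance only just above 30 ml/min (section 9.1). If investigators resolve the conflict differently, delays and reductions in Arm B will depend partly on who happened to test.

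**Working it through.** The protocol gives no figure for this, so the check is a count of cycle starts against scheduled visits.

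**Inputs**
- Cycle length 28 days, maximum 18 cycles (10.3.1).
- Visits every 3 months in years 1 and 2 (10.3.1 with 10.2; Table 4 bracket).
- CBC and RFT ticked at those visits up to 18 months (Table 4). Section 10.2 makes hemogram and renal tests as-needed in the observation arm's second year. That is not used here; the more generous Table 4 is.
- Assumptions: all 18 cycles are given without delay; visits are counted from treatment start; the baseline sample serves cycle 1.

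**Step 1: cycle starts needing clearance.** Cycles 2 to 18 give 17 re-treatment day 1s, at days 28k after the first dose for k = 1 to 17, that is days 28 to 476 (17 × 28 = 476).

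**Step 2: scheduled visits by day 476.** The protocol does not say how 3 months is counted, so three calendars are used:
- 12-weekly: days 84, 168, 252, 336, 420 (next 504)
- 13-weekly: days 91, 182, 273, 364, 455 (next 546)
- calendar months: about days 91, 183, 274, 365, 457 (next 548)

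Each gives five visits.

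**Step 3: day 1s with no scheduled result.** The protocol does not say how old a day-1 result may be, so the accepted age is varied. Entries are numbers out of 17.

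| Result accepted if taken | 12-weekly | 13-weekly | Calendar |
| --- | --- | --- | --- |
| on day 1 itself | 12 | 16 | 17 |
| up to 7 days before | 12 | 15 | 16 |
| up to 14 days before | 12 | 14 | 15 |
| up to 27 days before | 12 | 12 | 12 |
| up to 28 days before | 7 | 11 | 12 |

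With an age limit under one cycle, a visit can clear at most one day 1, so at least 17 − 5 = 12 are left. At 28 days, a sample taken on one day 1 can also clear the next, and the count falls. If a baseline sample drawn on the first dosing day also counts, the 28-day row becomes 6, 10 and 11.

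**Step 4: other choices.** Accepting any visit within 14 days on either side gives 12, 11 and 12, although a result obtained after day 1 cannot clear it. Section 10.1 allows treatment to start up to 30 days after registration. If the visit clock starts that much earlier, the 27-day count stays at 12, except for 12-weekly visits with a lag of 28 to 30 days, where a sixth visit falls by day 476 and the count is 11.

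**Step 5: the per-cycle reading.** If the first half of the Table 4 heading governs, every day 1 has a scheduled result and the count is 0 of 17.

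**Step 6: the two related statements.**
- Haemoglobin: 80 g/L = 8 g/dl, so the mg/dl in 10.3.4 is a unit error.
- Duration: 18 × 28 = 504 days. Eighteen months is 18 × 30.4375 ≈ 548 days. The gap is about 44 days, or 44/7 ≈ 6 weekly doses.

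**The case against.** **The table may already require per-cycle testing.** The first half of the Table 4 heading points that way. It agrees with 10.3.4 and the D1 rows of Table 1, and section 11.2 grades adverse events after each treatment cycle. Section 10.3.1 says only that visits are similar to Arm A's. This stands in part: the 3-monthly reading is the likelier one, not the only one. It does not rescue the text, because per-cycle testing would make the Table 4 bracket and the visit wording in 10.3.1 wrong instead.

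**The count depends on an age limit the protocol never sets.** This stands. A reader might take 12 of 17 as a fixed property of the design. It is not: one extra day of tolerance lowers it to between 7 and 12, and stricter matching raises it to as many as 17. What survives is that, with results younger than one cycle, most cycle starts have no scheduled result.

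**Nothing forbids extra tests.** True. Section 10.3.4 names each parameter and so tells the investigator to obtain it, and the delay rules imply repeat counts during a hold. A reader might infer that patients would be dosed without any monitoring between visits; the document does not say that. But a mandatory check should not rest on tests that the schedule leaves out.

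**Reported toxicity is low.** Section 4.6 cites no grade 3-4 events in one series and 3.8% grade 3 haematological toxicity in another, and the concept sheet cites below 5% internationally. These figures might justify 3-monthly testing, though they come from retrospective series, and the second used a different drug (S-1, section 4.5). They do not reconcile the rule with the schedule. The protocol gives no basis for estimating how many events would be missed, and none is claimed here.

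**Conclusion.** The contradiction is in the text and should be fixed. On the 3-monthly reading, five scheduled visits serve 17 cycle starts. The number without a recent scheduled result is 12 if results up to 27 days old are accepted, 12 to 15 within 14 days and 12 to 17 on the exact day; on the per-cycle reading it is 0. These figures assume 18 undelayed cycles and visits counted from treatment start.

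Confidence is high that the sections conflict and moderate that 3-monthly testing is what was meant. A reader might go on to infer a threat to the trial's main result. The documents do not support that: the overall survival comparison, the sample size and the type I error do not depend on the blood schedule. The haemoglobin unit and the duration mismatch are separate, smaller errors that do not bear on the monitoring count.

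**What to change.** Amend 10.3.1, 10.3.4 and the Table 4 heading so that they state one interval.

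- **Preferred:** schedule a local CBC and creatinine before each cycle, state how old the result may be, and keep outcome visits 3-monthly in both arms. This adds about 12 to 17 tests per Arm B patient who completes 18 cycles, depending on whether visit samples count. Assuming 1:1 allocation of the 1038 patients in 13.3.1 (519 in Arm B) and that all complete, the total is 519 × 12 = 6,228 to 519 × 17 = 8,823, roughly 6,200 to 8,800. Early stopping of treatment would lower it.
- **Alternative:** state that the day-1 criteria apply only at the 3-monthly visits and at symptom-triggered tests, and record why that is acceptable. This adds no tests. It removes the contradiction but leaves the long interval between counts.

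In the same amendment, change the haemoglobin threshold in 10.3.4 to 8 g/dl, and give one maximum duration in one unit in 10.3.1, the concept sheet and Table 4. The cost is one protocol amendment, with no change to the sample size, the analysis or the outcome calendar.

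### Section 10.3.4 bars day-1 re-treatment at a new grade 1 toxicity that 10.3.3 and six Table 2 rows allow, and its haemoglobin limit has the wrong unit

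*Protocol*

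**What the plan says.** Four places in the protocol govern when an arm B patient may be dosed again.

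- **Section 10.3.4** lists what day 1 of a new cycle requires. It includes "haemoglobin > 8 mg/dl" and resolution of "all non haematological toxicities (except alopecia and fatigue) to baseline or less than grade 1". It adds that if methotrexate is held while celecoxib goes on, the cycle counts as continued.
- **Section 10.3.3** holds treatment, as a general rule, for grade 3-4 events, "not restarted until the adverse event has resolved to G0-1", with investigator discretion. Its stopping rule is: "If the adverse event has not resolved to G0-1 after delaying day 1 treatment for 14 days, then study treatment should be discontinued". Its only exemption is: "Treatment should not be delayed or modified for alopecia of any grade".
- **Section 10.3.3.2, Table 2** gives "Restart when G0-1" in the rows for infection, nausea, vomiting, diarrhoea, mucositis and skin. The skin row holds both drugs: "Delay methotrexate and celecoxib until G0-1".
- **Section 10.4, item 3** ends study treatment after a 14-day delay caused by treatment-related adverse events. It names no grade.

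For haemoglobin, Table 1 (section 10.3.3.1) works in g/L and transfuses below 80. Section 11.1 uses g/dl.

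**The concern.** These are working thresholds for a self-administered methotrexate-celecoxib regimen of up to 18 cycles. If the day-1 rule asks for grade 0 while the toxicity table is content with grade 1, two clinicians who both follow the protocol can treat the same patient differently. The six-monthly audit of adherence (section 19) then has no single standard to apply. The stricter rule could also prolong a hold until the delay-based stop in 10.4 applies. The haemoglobin limit stands in the same sentence as a safety condition, so a wrong unit there leaves the condition empty.

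**Working it through.** **Grade limit.** Less than grade 1 is grade 0. Take a patient with no such toxicity at baseline, a grade 3 event in the previous cycle, and grade 1 on the next day 1:

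| Rule | Limit | Result on that day 1 |
| --- | --- | --- |
| 10.3.3 | grade 0-1 | restart allowed |
| Table 2, six rows | grade 0-1 | restart directed |
| 10.3.4 | baseline or grade 0 | barred |

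If the patient entered the trial with that toxicity at grade 1, the baseline clause is met and nothing conflicts.

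**Row count in Table 2.**
- Restart at grade 0-1: infection, nausea, vomiting, diarrhoea, mucositis, skin = 6.
- Discontinue: bilirubin, AST/ALT, myocardial infarction, arterial event = 4.
- Own limit: creatinine = 1.
- Physician discretion: venous event = 1.
- Total: 6 + 4 + 1 + 1 = 12, so 6 of 12 rows meet the conflict.

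**Stopping rule.** Suppose the event is still at a new grade 1 after 14 days.
- 10.3.3: grade 0-1 has been reached, so no discontinuation.
- 10.3.4: day 1 is still barred.
- 10.4 item 3: a 14-day delay from a treatment-related event, so discontinuation can apply.

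This route is clearest in the skin row, where both drugs are held. Where celecoxib continues, 10.3.4 itself treats the cycle as continued.

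**Haemoglobin.**
- As written: 8 mg/dl x 10 dl/L = 80 mg/L = 0.08 g/L.
- Table 1: 80 g/L, and 80 / 10 = 8 g/dl.
- Ratio: 80 / 0.08 = 1000.

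The limit of 10.3.4 does not reproduce that of Table 1. With g in place of mg it matches exactly.

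**Exempt list.** 10.3.3 exempts alopecia; 10.3.4 exempts alopecia and fatigue.

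**The case against.** The case for leaving the text alone is substantial, and part of it stands.

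- *The intent is obvious.* The rest of the dosing section uses grade 0-1, so grade 1 or less was probably meant, and nobody would apply 0.08 g/L literally. This is likely true. It is a reason to correct the sentence, because 10.3.4 is phrased as a requirement.
- *The sections can be reconciled.* Grade 0 lies within grade 0-1, and 10.3.3 is a general rule with discretion, so waiting longer breaches nothing in 10.3.3. That holds for 10.3.3. The six Table 2 rows direct a restart and carry no such qualifier.
- *They govern different moments.* 10.3.4 concerns day 1 of a cycle and handles mid-cycle restarts separately. This stands: the clash arises only on a day 1. Arm B visits are also three-monthly, which gives 18 / 3 = 6 scheduled visits over 18 months against up to 18 day 1s, so many day 1s have no scheduled clinic assessment.
- *A tie-breaker exists.* 10.3.3 says that for "several adverse events with differing recommendations, then the modification that results in the longest delay and lowest dose should be used". That sentence covers one patient with several events. It does not rank two sections that differ over one event.
- *Fatigue.* A reader might infer that the two exempt lists give opposite orders for grade 3 fatigue. They do not. 10.3.4 states necessary conditions, so holding under 10.3.3 satisfies both. The wording is merely unaligned.
- *Grade 2.* A reader might think that a new grade 2 event on day 1 is left open. It is not: 10.3.4 bars day 1 for it, before and after correction.

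**Conclusion.** Wrong as written, minor, and confined to arm B dosing. Two statements in one sentence of 10.3.4 need correcting: the grade limit, which conflicts with six Table 2 rows for a grade 3-4 event that has come down to an above-baseline grade 1 on a day 1, and the haemoglobin unit.

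Three stronger readings are not supported.

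- *A count of affected patients.* The concept sheet puts grade 3-4 side effects below 5% in international studies and at none in the retrospective methotrexate-celecoxib study. With 1038 patients and 1:1 allocation assumed, 5% x 519 is about 26. That figure includes haematological events and rows outside the conflict, and it ignores whether the event sits at a new grade 1 on a day 1. It does not measure the affected group. The protocol gives no grade 1 rates, so no estimate is possible.
- *Widespread premature discontinuation.* The route needs a treatment-related event, a 14-day hold, and a reading of 10.4 item 3 apart from the more specific rule in 10.3.3.
- *Loss of the anaemia safeguard.* Table 1 directs transfusion below 80 g/L regardless of the slip.

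There is no effect on sample size, power or the survival analysis.

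**What to change.** In 10.3.4, write *haemoglobin > 8 g/dl (80 g/L)* and *to baseline or grade 1 or less*. As tidying, use one exempt list in 10.3.3 and 10.3.4: alopecia, with fatigue added to both only if that is intended. The Table 2 rows can stay as they are. No separate grade 2 statement is needed, because the corrected wording already bars day 1 for a new grade 2 event.

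The cost is one sentence in 10.3.4 and, at most, one matching phrase in 10.3.3, made by protocol amendment. Design and sample size do not change.
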